### Procedure

#### Recruitment, baseline assessment and randomization

A depression experience expert (author PO) provided input on the intervention and application procedure before the start of the trial. The recruitment and assessment process is illustrated in a flowchart shown in Fig. 1. Clinicians will provide eligible candidates with basic information about the study on paper and/or through an informative video. Clinicians will only inform patients capable of consenting to participation. Interested candidates are referred to the researchers who will provide further information by phone. Eligible participants will be asked to provide their written and informed consent for participation at their first visit to the treatment site, where they will subsequently complete the baseline assessment (T0) gauging depressive symptoms, cognitive functioning, rumination, cognitive emotion regulation, quality of life, and health-care consumption, and health-related disability (economic evaluation). If inclusion criteria are satisfied, participants are randomly assigned to the intervention (CCT) or the active control condition (placebo training) by computer-generated allocation stratified for depression severity as assessed with the Inventory of Depressive Symptomatology Self Report: mild (IDS-SR < 38), moderate (IDS 39–48) and severe (IDS > 49) [52]. At the end of the baseline assessment, all participants are provided with a digital tablet to enable them to complete the eight training sessions in their own homes. Researchers will explain, demonstrate and practice the use of the tablet and schedule the training sessions together with the participant. During the one-month training period, participants will receive email notifications to remind them of the task, while researchers will regularly contact them by phone to monitor their progress, with the number and timepoint of the telephone contacts being documented for each participant.

**Fig. 1 Fig1:**
[figure not shown]
CONSORT flow chart

Approximately 1 month after the training, a post-training evaluation (T1) will be conducted including all but three of the baseline measurements. For an overview of the measurements and their timepoints, we refer to Table 1. Participants are asked whether any changes have occurred in the LLD treatment during the training period. Participants that did not complete all training sessions will also be asked to complete all post- and follow-up assessments.

**Table 1 Tab1:** Overview of measures and corresponding timepoints

Measure	Target concept	Baseline (T0)	Post-training (T1)	FU-1 (T2)	FU-2 (T3)	FU-3 (T4)
**IDS-SR**	Severity of depressive symptoms	●	●	●	●	●
**RRS**	Trait rumination	●	●			
**BFT**	State rumination	●	●			
**CERQ**	Cognitive emotion regulation strategies	●	●			
**PASAT**	Working memory capacity	●	●			
**RNG Task**	Working memory capacity	●	●			
**STROOP**	Inhibition of interfering stimuli	●	●			
**MOCA**	Cognitive dysfunction	●				
**EQ-5D-5l**	Health-related quality of life	●		●	●	●
**WHODAS 2.0**	Functioning and disability	●	●	●	●	●
**TiC-P**	Health-care costs (in the Netherlands) based on self-reported health consumption and productivity loss	●			●	●

*IDS-SR* Inventory of Depressive Symptomatology, *RRS* Ruminative Response Scale, *BFT* Breathing Focus Task, *CERQ* Cognitive Emotion Regulation Questionnaire, *PASAT* Paced Auditory Serial-Addition Task, *RNG task* Random Number Generation task, *Stroop task* (i.e. inhibition of interfering stimuli), *MOCA* Montreal Cognitive Assessment, *EQ-5D-5L* (i.e. quality of health), *WHODAS* World Health Organization Disability Assessment Schedule, *TiC-P* Trimbos Institute and iMTA Cost questionnaire for Psychiatry (i.e. economic costs)

Participants will again fill out the questionnaires 3, 6 and 12 months (T2, T3, and T4) post-training. Health-care utilization data will be collected with the TiC-P at T0, T3 and T4. The qualitative interviews for the flanking implementation study will be conducted between the post-training and 3-month follow-up. For a complete overview of the study design, we refer to Fig. 1.

Because of the COVID-19 pandemic, we created an online version of the original study procedure to enable us to safely test participants. The baseline and post-training assessment were, during the height of the pandemic, administered by telephone and participants were sent the information and materials needed to complete the training tasks and questionnaires by email, with instructions on how to open the files and how and when to perform the tasks and measurements being provided by telephone. The participants’ performance and responses were monitored and documented by the task leader throughout the training period. We resumed testing at the sites, as soon as the national COVID-19 guidelines and protocols of the participating centers permitted us to. Safety measures included the use of plastic screens between test leaders and participants, the use of gloves, and wearing face masks at all times.

### Ethics

The study has been approved by the regional Medical Ethical Committee Arnhem-Nijmegen, the Netherlands (trial number NL67671.091.180). This trial is registered in the Netherlands Trial Register (code: NL7639). The study protocol adheres to CONSORT guidelines (Moher, Schulz, Altman, & Group, 2001). Data will be processed confidentially, with only the principal and coordinating investigators having access to confidential information. Monitoring of the research process will be done regularly, by an independent monitor. Data management is overseen by an independent data management officer.

Adverse events will be defined as any undesirable experiences participants may undergo during the study, irrespective of whether they are (considered to be) related to the CCT or placebo training. All spontaneously reported adverse events and those observed by the investigator will be recorded. Serious, potentially life-threatening events will be reported to the ethics committee within 7 days.

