The adaptive Paced Auditory Serial Addition Task (aPASAT) is a promising intervention aimed at enhancing cognitive control [24, 56]. In this task, individuals are instructed to sum up the last two numbers they heard in an auditorily presented continuous stream of numbers. It is adaptive in that its presentation speed is continuously matched to the participant’s performance, inducing greater emotional reactivity (e.g., frustration, negative thoughts, some negative affect), which might account for the benefits derived from such tailored tasks [11, 17]. Siegle et al. [56] concluded that the aPASAT activates the cognitive control network by showing that the dorsolateral prefrontal cortex is engaged during its performance. They also tested the task in participants with MDD, in whom the cognitive training reduced depressive symptoms and rumination more so than was the case in a control group receiving treatment as usual (TAU) [56]. Further studies continued to show beneficial effects of the aPASAT on depressive symptoms in various samples, where gains were possibly mediated by diminished rumination through improved cognitive functioning [12, 53, 60]. Interestingly, Brunoni et al. [12] observed, in a combined treatment group receiving CCT and transcranial direct-current stimulation, that sustained reduction in depressive symptoms was greatest in the older participants, even when controlling for changes in cognitive control throughout the training. This suggests that especially older depressed adults benefit from the aPASAT as an add-on to other treatment.

In summary, there is an urgent need for innovative, effective, and affordable treatments for LLD, which can be delivered alongside treatment as usual. The literature indicates that adaptive CCT approaches may be most effective in improving cognitive functioning and reducing rumination in older adults. The aPASAT is a relatively low-cost intervention that can be used as an add-on treatment to TAU, but large-scale clinical trials investigating its (cost-)effectiveness, working mechanisms, and feasibility in LLD are lacking. We aim to address these questions in the RCT described below.

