## Methods

### Design

Our study comprises a single blind RCT with a between-subjects design and two conditions. Participants are randomly allocated to the intervention condition (CCT) or the active control condition (placebo training). Qualitative interviews will be conducted in two subgroups of participants in the intervention arm.

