#### Depressive symptoms

##### Ids-SR

The Dutch version of the Inventory of Depressive Symptomatology Self Report [52] will be used to assess the severity of depressive symptoms. It consists of 30 items covering various symptom domains of depression. Apart from the baseline measurement (T0), the questionnaire will be administered within 1 month after CCT completion (T1) to measure the direct effects of CCT, and at three follow-up timepoints (T2, T3, and T4) to evaluate the longer-term effects (up to 12 months). Treatment response will be defined as a 50% IDS-SR symptom reduction between baseline and 12-month follow-up. Depression remission will be defined as an IDS-SR score of ≤14.

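### Adverse events are recorded only if volunteered or noticed, so counts risk being too low and unequally ascertained between arms

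*Protocol article*

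**What the plan says.** The adverse-event text is in the Ethics section of the protocol article. The definition is wide: "Adverse events will be defined as any undesirable experiences participants may undergo during the study", whether or not linked to the training. The capture rule is narrower: "All spontaneously reported adverse events and those observed by the investigator will be recorded". Expedited reporting covers a small subset: "Serious, potentially life-threatening events will be reported to the ethics committee within 7 days". Table 1, which lists the measures by timepoint, has no adverse-event instrument.

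Several other sections bear on how this rule would work:

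- **Setting and contact** (Recruitment, baseline assessment and randomization): the eight sessions are done at home on a tablet. During the training month "researchers will regularly contact them by phone to monitor their progress". The number of calls is not fixed, but number and timing are logged for each participant.
- **Expected reaction** (Background): the adaptive task matches its speed to performance, "inducing greater emotional reactivity (e.g., frustration, negative thoughts, some negative affect"). The placebo task asks only for the last digit heard and does not load working memory (Placebo training).
- **First measure after baseline**: T1, placed about one month after training in the Procedure text and within one month of completion in the IDS-SR section. Both are after the training has ended.
- **Contact in one arm only**: the Design section places the qualitative interviews in the intervention arm. The Implementation study section plans 16 to 20 of them, covering experienced effects among other topics, and adds two satisfaction questions at T1 for the experimental group.

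**The concern.** The definition and the capture rule do not match. A definition that takes in any undesirable experience needs someone to ask. Spontaneous reporting finds what a participant thinks worth mentioning and has an occasion to mention. Investigator observation adds little when sessions take place at home and T2 to T4 are questionnaire points.

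Two features make this more than a matter of low counts. First, the document itself foresees an unpleasant reaction that belongs to one arm and arises during the training weeks, when no scheduled instrument is administered. Second, some contact in which an event could be volunteered exists in the CCT arm only. If capture differs between arms, the counts mix what happened with how likely it was to be heard. The article plans no between-arm test of adverse events, but any harms statement would rest on these counts, and the authors hope the training will enter treatment guidelines.

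**Working it through.** The protocol gives no adverse-event rate, power or analysis, so there is no stated figure to reproduce. The check is a comparison of the text, followed by illustrations on declared assumptions.

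**1. What is asked of both arms, and when.** The IDS-SR and WHODAS 2.0 are collected at T0 to T4 in both arms. The RRS and the breathing focus task are collected at T0 and T1. None falls within the four training weeks, so distress that arises in sessions and has passed by T1 is picked up only if volunteered or noticed.

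**2. Contact given to one arm only.** Interviews: 16 to 20. Planned CCT arm: 52 (Sample size calculation). If all interviewees come from those 52, 16/52 = 31% and 20/52 = 38% of CCT participants have an in-depth conversation that no placebo participant has.

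**3. Effect of unequal capture (capture rates assumed).** Recorded risk ratio = true risk ratio × (capture in CCT ÷ capture in placebo). With no true difference, a true risk of 20% in each arm, 52 per arm and 50% capture under placebo, the expected placebo count is 52 × 0.20 × 0.50 = 5.2.

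| Capture in CCT | Expected CCT count | Recorded risk ratio |
|---|---|---|
| 50% | 52 × 0.20 × 0.50 = 5.2 | 1.0 |
| 60% | 52 × 0.20 × 0.60 = 6.2 | 1.2 |
| 70% | 52 × 0.20 × 0.70 = 7.3 | 1.4 |
| 90% | 52 × 0.20 × 0.90 = 9.4 | 1.8 |

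In the other direction, a true ratio of 1.5 with CCT capture at two thirds of placebo capture is recorded as 1.5 × 2/3 = 1.0.

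**4. Effect of low but equal capture (assumed).** The ratio is unbiased but information is lost. For true risks of 10% and 30%, a two-sided 5% test of two proportions with 52 per arm has power 0.73. At 50% capture in both arms the recorded risks are 5% and 15%, and power is 0.40. If no events are recorded among 52, the exact one-sided 95% upper limit is 1 − 0.05^(1/52) = 5.6% under full capture, but about 0.056/0.40 = 14% if only 40% of events surface.

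**5. Precision of a worsening table (rate assumed).** At 15% worse in each arm, the 95% half-width for the difference is 1.96 × √(2 × 0.15 × 0.85/52) = 0.137, about 14 percentage points.

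**The case against.** The strongest reply is that the plan collects a good deal that bears on harm, on a fixed schedule and alike in both arms. The IDS-SR and WHODAS 2.0 run from T0 to T4. The mixed model (Evaluation of clinical outcomes) uses all four post-baseline assessments with baseline as covariate, so worsening enters the main result. Participants are asked about treatment changes during training, reasons for drop-out are assessed systematically, and all are under clinical care. A reader might infer that the trial could not compare harm fairly, or could not say whether patients got worse. The documents do not support that. What remains is narrower: these measures do not cover events other than symptoms and disability, or distress that has passed by T1. The patient-level IDS-SR outcomes also do not separate worsened from unchanged patients: "Treatment response will be defined as a 50% IDS-SR symptom reduction between baseline and 12-month follow-up", and remission is a low score.

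A reader might also infer that the harder task brings more calls, so that CCT participants have more chances to report. Nothing says that the calls differ by arm or that they are the adverse-event channel; they are for monitoring progress. Likewise, "Our study comprises a single blind RCT" does not say who is blinded, so it cannot be taken as stated that those recording events know the allocation.

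The Background does not present the emotional reactivity as a harm; it offers it as a possible source of benefit. That is fair, but a reaction can be both a mechanism and an undesirable experience under the article's own definition.

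Finally, the article condenses a fuller protocol that may add procedures. The point does not rest on missing detail, however: the capture method is stated, and as stated it is passive.

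**Conclusion.** The point holds as a risk of under-ascertainment and of unequal ascertainment in the adverse-event counts. It rests on text: a passive capture rule under a broad definition, home training, a foreseen reaction specific to the active task, no scheduled measure until training is over, and interviews and extra questions in one arm only.

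Its size cannot be derived from the document, and the bias could run either way. The ratios of 1.2 to 1.8, and the masking of a true 1.5, follow wholly from assumed capture rates; they show what is possible, not what is expected. The primary analysis of depressive symptoms is not affected, and deterioration in depression and disability remains comparable between arms from data already planned. This should be changed because the remedy is cheap, not because the trial's main conclusion is in danger.

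**What to change.** In the Ethics section, replace the capture sentence with a rule along these lines: every participant in both arms is asked the same open adverse-event question at the same fixed times, namely one set call during the training period and T1, T2, T3 and T4, by staff blind to allocation where possible. Record spontaneously reported events, and events first raised in the CCT-only interviews, separately by source, so that the elicited events can be compared like with like. Add the question as a row in Table 1. The account of pandemic testing is in the past tense, so assessments had evidently begun; if the change comes during recruitment, report events by ascertainment method and do not pool them silently.

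Also tabulate by arm, from the IDS-SR already collected, the proportion worse than baseline at each of T1 to T4, using a point increase fixed in advance. A move to a higher randomisation severity band would not serve: it cannot register worsening in anyone already severe at baseline, and the bands as printed (below 38, 39 to 48, above 49) leave scores of 38 and 49 unassigned.

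The cost is one question at existing contacts, one fixed call and one extra table. More minor events will be recorded than under spontaneous reporting, and the worsening comparison will be imprecise, so it should be presented as an estimate with its interval.

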### Interventions

#### aPASAT training

In the adaptive Paced Auditory Serial Addition Task participants are asked to give the sum of the last two numbers of a continuously presented auditory stream of digits (1–9) and type in the corresponding number (2–18) on the tablet screen. Each training session starts with an interstimulus interval (ISI) derived from the participant’s baseline performance, which interval is subsequently adjusted based on his/her current performance to thus modify task difficulty: following four consecutive accurate or inaccurate answers, the ISI is adjusted with +/− 100 ms, after which the training speed is adapted to the participant’s present response speed. Each session consists of 400 trials corresponding to 20 min training time if the average ISI is 3000 ms; training times can thus vary dependent on participants’ response speed.

#### Placebo training

Participants in the control group will be presented with an active placebo training whose duration, frequency and presentation matches the actual CCT. However, participants will only be asked to tap the number on the touch screen that corresponds to the last heard digit, thus not loading working memory. Research has shown this to be a reliable control condition for the active CCT intervention [35].

#### Measures

Table 1 provides an overview of all measurements and their timepoints.

#### Depressive symptoms

##### Ids-SR

The Dutch version of the Inventory of Depressive Symptomatology Self Report [52] will be used to assess the severity of depressive symptoms. It consists of 30 items covering various symptom domains of depression. Apart from the baseline measurement (T0), the questionnaire will be administered within 1 month after CCT completion (T1) to measure the direct effects of CCT, and at three follow-up timepoints (T2, T3, and T4) to evaluate the longer-term effects (up to 12 months). Treatment response will be defined as a 50% IDS-SR symptom reduction between baseline and 12-month follow-up. Depression remission will be defined as an IDS-SR score of ≤14.

#### Rumination and cognitive emotion regulation

##### RRS

The Ruminative Response Scale (RRS) will be used to assess trait rumination [46] at T0 and T1. The Dutch version contains 22 items and demonstrated good internal consistency.

##### BFT

The breathing focus task [28], also administered at T0 and T1 only, serves to measure state rumination. Participants are asked to close their eyes and focus on their breathing for 5 minutes. Throughout, they will hear 12 random sound signals and after each signal they are asked to report whether they are focusing on their breathing. If they are not, they are to rate the nature of the intrusion as positive, negative, or neutral, and describe the thought briefly (e.g., negative - my depression). The number of negative intrusions reflects the severity of rumination.

##### CERQ

To gauge the participants’ cognitive strategies to deal with emotions, the cognitive emotion regulation questionnaire [23] will be used. Its 36 items are divided into nine subscales. In each subscale, the respondent needs to indicate his/her reaction to the threatening or stressful life event that is described. They will complete the CERQ at T0 and T1.

#### Cognitive functioning and emotional inhibition

##### PASAT

A non-adaptive version of the PASAT will be included as a measure of task-specific transfer of the CCT [24]. Comparable to the aPASAT, participants are presented with a continuous auditory stream of numbers of which they have to add the two last-heard digits. The task is presented in three trial blocks with ISIs of 3000, 2000, and 1500 ms, respectively. The task will be completed at T0 and T1.

##### RNG

The random number generation task will serve as an indicator of working memory capacity [48] and prefrontal functioning. Participants are asked to generate numbers sequentially, usually at a rate of one per second, and instructed to avoid ordered sequences (e.g., 1, 2, 3, 4, or 3, 5, 7, 9). Allowable responses are restricted to a specified range (e.g., 1–10). Instructions to the task are follows: “What I would like you to do is attempt to generate a random sequence of numbers between 1 and 10. Imagine, if you will, having these numbers written on pieces of paper placed in a hat. Shake the hat, draw out a piece of paper and read the number. Then put the paper back into the hat, shake it again, and draw another number out, and continue this process”. The task leader notes the responses and response times on an answer sheet. A participant’s working memory capacity is determined by the response times and randomness of the answers given [7], and is related with prefrontal functioning. The RNG is administered at T0 and T1.

##### Stroop task

The task [64] assesses whether participants are able to inhibit attention to interfering stimuli. We will be using both the classical and an emotional Stroop task. In the former task, participants are shown both congruent stimuli (e.g., the word ‘green’ presented in a green color) and incongruent stimuli (e.g., the word ‘green’ presented in a yellow color) on a laptop and instructed to name the color in which the words are presented as fast and as accurately as possible. Three screens are presented: a congruent and an incongruent screen and one with strings of letters printed in different colors (red, yellow, green and blue) that are presented in 12 rows of 4 words providing an index of basic color naming speed. The screens are presented in random order to avoid order effects. The researcher measures the time per screen with a stopwatch. Response times and accuracy serve as measures of inhibition ability.

In the emotional Stroop task words of different valence (i.e., positive, negative, or neutral) are presented in different colors (red, yellow, green, and blue). Words and valances are derived from two databases of Dutch words [10, 41] with one extra neutral word added. The words are presented in a similar manner to the classical Stroop task. The difference in response times and accuracy rates between the dissimilarly valenced cards indicates the participant’s cognitive ability to inhibit task-irrelevant emotional information.

